# Clinical and virological outcomes with baloxavir compared with oseltamivir in pediatric patients aged 6 to < 12 years with influenza: an open-label, randomized, active-controlled trial protocol

**DOI:** 10.1186/s12879-021-06494-w

**Published:** 2021-08-09

**Keywords:** Baloxavir, Child, Clinical trial protocol, Influenza, Japanese, Oseltamivir

## Abstract

**Background:**

Children with influenza virus infections are prone to complications and are common sources of influenza transmission. Baloxavir marboxil inhibits cap-dependent endonuclease and was approved for influenza treatment in adolescent, adult, and pediatric patients in Japan. The miniSTONE-2 study included pediatric patients with influenza (1 to < 12 years) and demonstrated similar median times to alleviation of signs and symptoms of influenza with a single dose of baloxavir granules (weight < 20 kg: 2 mg/kg, ≥ 20 kg: 40 mg) and oseltamivir. Although the baloxavir dose in miniSTONE-2 was higher than the Japanese-approved dose, baloxavir exposure in miniSTONE-2 was similar to Japanese pediatric patients who receive the Japanese-approved dose. This study will be the first randomized active-controlled study in pediatric patients with influenza using the Japanese-approved dose of baloxavir.

**Methods:**

This is a multicenter, open-label, randomized, active-controlled trial in which 200 Japanese subjects aged 6 to < 12 years with influenza virus infection are randomly allocated (2:1) to a single dose of baloxavir at the approved dose in Japan (weight ≥ 10 to < 20 kg: 10 mg, ≥ 20 to  < 40 kg: 20 mg, ≥ 40 kg: 40 mg) or oseltamivir twice daily for 5 days. The primary clinical endpoint is the time to illness alleviation of influenza, from administration of baloxavir or oseltamivir until the following criteria were met and sustained for at least 21.5 h (24 h—10%): cough and nasal discharge/nasal congestion rated as absent or mild axillary body temperature < 37.5 °C. The primary analysis population is the intention-to-treat infected population, which includes all pediatric subjects who receive at least one dose of study drug and have confirmed influenza virus infection by reverse transcription-polymerase chain reaction. The safety population includes all subjects who receive at least one dose of study drug.

**Discussion:**

No comparative studies have been conducted to confirm the efficacy and safety of baloxavir versus a comparator in pediatric patients with influenza infection in Japan. The outcomes from this trial will provide evidence on the efficacy and safety of baloxavir as an antiviral treatment option for Japanese pediatric patients with influenza infection. *Trial registration* Japan Registry of Clinical Trials: jRCTs011200011. Registered November 2020. (https://rctportal.niph.go.jp/en/).

## Background

Influenza virus infections commonly occur in children and can be associated with serious complications such as febrile seizures and influenza encephalopathy, and significant socioeconomic burden [1–4]. Globally, influenza infection is estimated to be responsible for 16% of hospitalizations for respiratory disease among children 5–17 years [3] and 5% of hospitalizations for acute lower respiratory disease among children < 5 years [5]. Similarly, in Japan, approximately 25% of influenza infections occur in children 6–12 years, and hospitalizations due to severe influenza-related complications are higher in children than adults and are highest in children < 5 years [6]. Preventing influenza infection in children is particularly important because they are a common source of influenza transmission among households and the wider community [7, 8]. While annual vaccination is the most effective means of preventing influenza and influenza-related complications [1], effectiveness is limited by the emergence of new influenza virus subtypes, the increased susceptibility of children to influenza infection, and decreased vaccine coverage and availability [9–11].

Neuraminidase inhibitors (NAIs) are recommended for the treatment of influenza virus infection in children who are critically ill or at high risk of complications, are symptomatic and have household members who are at high risk of developing influenza complications, and are within 2 days of symptom onset [1]. In children, NAIs have been shown to reduce the duration of influenza illness [12] and the incidence of influenza-associated acute otitis media [13], and may contribute to improved survival in those who are critically ill [14]. However, there may be differences in the effectiveness of NAIs across influenza types in young children (1–5 years) as shown by oseltamivir, which is less effective against influenza type B virus than influenza type A virus [15]. In addition to intrinsic factors such as age and immune status, other factors that may contribute to reduced effectiveness include nonadherence to a repeat-dose treatment regimen or difficulties with inhaled routes of administration [16, 17]. Further, emerging resistance to current NAIs indicates that new antiviral treatments with different mechanisms of action are needed to complement the currently available options for antiviral therapy [18, 19].

Baloxavir marboxil (hereafter termed baloxavir) is an oral antiviral prodrug in which the metabolite, baloxavir acid, selectively inhibits the cap-dependent endonuclease activity of the influenza type A and B polymerase acidic protein (PA) protein [20, 21]. In Japan, baloxavir is approved for the treatment of influenza in adolescents and adults, and in pediatric patients. In adolescents and adults aged 12–64 years with uncomplicated influenza, single-dose baloxavir significantly improves time to alleviation of influenza symptoms compared with placebo and significantly reduces infectious virus titer compared with placebo and oseltamivir (CAPSTONE-1) [22]. In addition, in high-risk adolescents and adults (12–89 years) with uncomplicated influenza, early treatment with baloxavir has been shown to reduce influenza-associated complications compared with placebo (CAPSTONE-2) and also significantly shorten the time to improvement of influenza symptoms compared with oseltamivir in patients with influenza type B [23]. The efficacy and safety of baloxavir 2% granules for oral suspension have been assessed in a double-blind, randomized, active-controlled trial in non-Japanese children aged 1– < 12 years with influenza (miniSTONE-2) [24]. In this study, a single dose of baloxavir granules (2 mg/kg for those weighing < 20 kg and 40 mg for those weighing ≥ 20 kg) was similarly effective at alleviating signs and symptoms of influenza compared with oral oseltamivir administered twice daily for 5 days, and baloxavir shortened the median time to cessation of viral shedding compared with oseltamivir. Although the dose of baloxavir in miniSTONE-2 was higher than the dose that is approved for children in Japan (10 mg for those weighing 10 to < 20 kg and 20 mg for those weighing 20 to < 40 kg), studies of baloxavir in Asian and non-Asian individuals [25, 26] suggest that baloxavir exposure in the miniSTONE-2 study was similar to Japanese individuals who are administered the Japanese approved dosage. Two open-label noncomparative studies in Japanese children have been conducted, which showed that a single weight-adjusted dose of baloxavir granules [27] or tablet (in accordance with the approved dose regimen) [28] is well tolerated and appears to be clinically and virologically effective. In addition, findings from a large postmarketing surveillance study enrolling more than 3000 patients in Japan showed that the median time to alleviation of influenza symptoms in the pediatric population aged 6 to < 12 years of age (n = 703), was similar to that in adults [29]. However, no randomized active-controlled studies comparing baloxavir with oseltamivir have been conducted in a Japanese pediatric population at the Japanese approved dose of baloxavir.

This open-label randomized controlled trial was designed to assess the clinical and virological efficacy and tolerability of single-dose baloxavir compared with oseltamivir twice daily for 5 days for the treatment of influenza infection in Japanese children aged 6 to < 12 years.

## Methods

### Trial design

This is a multicenter, open-label, randomized, active-controlled trial of the clinical and virological efficacy of a single oral dose of baloxavir compared with oral oseltamivir twice daily for 5 days in otherwise healthy subjects aged 6 to < 12 years with influenza during the 2020–2021 influenza season in Japan. The trial, which started in November 2020, will enroll patients from approximately 82 pediatric clinics or pediatric hospital departments in Japan.

The trial protocol was reviewed/approved by the Hokkaido University Certified Review Board (CRB; approval number 020-005, October 2020). The trial will adhere to the Clinical Trials Act (Act No. 16, April 14, 2017), the Declaration of Helsinki, and Ethical Guidelines for Medical and Health Research Involving Human Subjects in Japan, and has been registered at the Japan Registry of Clinical Trials (https://rctportal.niph.go.jp/en/; jRCTs011200011).

All pediatric subjects will receive adequate information about the nature, purpose, and possible risks and benefits of the trial and about alternative therapeutic choices via a parent or legal guardian who will be provided with an informed consent form approved by the CRB. Every effort will be made to obtain written informed assent from each patient in accordance with their level of comprehension. Written informed consent will be obtained from a parent/legal guardian for each enrolled subject and every effort will be made to obtain written informed assent from pediatric subjects according to their capabilities. A subject and a parent/legal guardian will be free to withdraw from the trial at any time upon request. An investigator may terminate a pediatric subject’s participation in the study if the subject meets a newly developed or not previously recognized exclusion criterion that precludes further participation.

Eligible subjects will be registered and randomly allocated (2:1) to the baloxavir and oseltamivir groups using an interactive web response system (Fig. 1). Randomization will be stratified using stochastic minimization to balance age (≥ 6 to < 9 years, ≥ 9 to < 12 years) and baseline total score for the Influenza Symptom Severity Scale for respiratory symptoms (cough and nasal discharge/nasal congestion) (≤ 3, ≥ 4). The Influenza Symptom Severity Scale is rated by subjects or with assistance from a parent/guardian on a 4-point scale (0 = no symptoms, 1 = mild, 2 = moderate, 3 = severe). All study drugs will be administered by the subjects themselves or with assistance from a parent/guardian.

**Fig. 1 Fig1:**
[figure not shown]
Trial timeline

Screen failures are defined as pediatric patients who do not meet the eligibility criteria. Reasons for discontinuation from the trial will include the following: decision to discontinue by a pediatric subject or their parent/legal guardian; death or any serious adverse event (SAE) or intolerance to study drug as determined by the investigator; a positive severe acute respiratory syndrome coronavirus 2 (SARS-CoV-2) test or suspected coronavirus disease 2019 (COVID-19); any repeated deviation from the protocol (e.g. repeated use of concomitant prohibited drugs) for the duration of the trial; or any other reason as determined by the investigator.

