### Trial participants

Inclusion and exclusion criteria are described in full in Table 1. To be included in the trial, written informed consent from a parent/legal guardian will be required for each pediatric subject enrolled (every effort will also be made to gain written informed assent). In addition, pediatric subjects are to be otherwise healthy, aged 6 to < 12 years with a body weight ≥ 10 kg, have a positive rapid influenza diagnostic test which detects an antigen of influenza virus, and be judged by the investigator or sub-investigator to be able to take baloxavir tablet(s) and oseltamivir capsules or dry syrup. The main exclusion criteria are severe influenza symptoms requiring inpatient treatment, administration of systemic corticosteroids or immunosuppressive therapy, presence of an infectious disease requiring systemic antimicrobial therapy at the time of screening, allergies and/or a history of clinically problematic intolerance to anti-influenza drugs and/or acetaminophen, or a positive SARS-CoV-2 diagnostic test or suspected COVID-19 disease at the time of screening.

**Table 1 Tab1:** Inclusion and exclusion criteria

Inclusion criteria	
Age 6 to < 12 years	
Body weight ≥ 10 kg	
Diagnosed with influenza infection defined as: Fever (axillary temperature ≥ 38 °C) A positive RIDT by nasopharyngeal swab, pharyngeal swab, or nasal discharge At least one moderate or severe respiratory symptom (cough and nasal discharge/nasal congestion)	
Onset of first confirmed fever (≥ 37.5 °C) no more than 48 h before screening (Day 1)	
Judged by the investigator as able to take baloxavir tablet(s) and oseltamivir capsules or dry syrup	
Where possible, written informed assent from children Written informed consent from a parent or legal guardian	
Parents/guardians willing and able to comply with the trial requirements Patients who can comply with the trial requirements to the level of their understanding	
Exclusion criteria	
Severe influenza symptoms requiring hospitalization	
Risk factors for influenza infection including: Chronic respiratory diseases including uncontrolled bronchial asthma Hepatitis, liver cirrhosis Neurological disorders and neurodevelopmental disorders including brain, spinal, peripheral, and muscle disorders Endocrine disorders including diabetes, thyroid disease, and adrenal gland abnormalities Heart disease requiring drug treatment including congenital heart disease, congestive heart failure, and coronary artery disease	

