Receiving systemic corticosteroids or immunosuppressive therapy	
Primary immunodeficiency syndrome	
Severe renal impairment (creatinine clearance < 30 mL/min or eGFR < 30 mL/min/1.73 m^2^)	
Human immunodeficiency virus infection	
Malignant disease within the past 5 years	
Disorders of consciousness including abnormal behavior^a^ and convulsions, and complicated by encephalitis/encephalopathy	
History of encephalitis/encephalopathy or epilepsy not controlled with antiepileptic drugs or abnormal behavior^a^ associated with influenza infection in the past 2 years	
Infectious diseases requiring systemic antimicrobial therapy and/or antiviral medicine (except anti-influenza medicine) at screening	
Considered by the investigator to be using prohibited drugs	
Receiving baloxavir, amantadine, or NAIs (oseltamivir, zanamivir, peramivir, and laninamivir) within 30 days before screening	
History of allergies to anti-influenza drugs, or acetaminophen, or clinically problematic intolerance	
Positive SARS-CoV-2 or suspected COVID-19 disease	
Any underlying disease that may affect study outcomes	
Difficulty collecting blood from a vein Patients received an investigational or unapproved drug within 30 days or 5 half-lives, whichever is longer, before screening Patients with diseases or conditions which, in the opinion of the investigator, may make it difficult to ensure patient safety or study data quality Patients who, in the opinion of the investigator, are inappropriate for participation in the study Female patients who has experienced menarche and who are pregnant, plan to become pregnant during the study period, or are breastfeeding	

^a^Actions such as a sudden start, jump, or any other unexpected behavior that may be life-threatening

*COVID-19* coronavirus disease 2019; *eGFR* estimated glomerular filtration rate; *NAI* neuraminidase inhibitor; *RIDT* rapid influenza diagnostic test; *SARS-CoV-2* severe acute respiratory syndrome coronavirus 2

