### Outcome measures and endpoints

The primary clinical endpoint is the time to illness alleviation (TTIA), defined as the time from baloxavir or oseltamivir administration until the following criteria were reached and sustained for at least 21.5 h (24 h—10%): both cough and nasal discharge/nasal congestion assessed as 0 (absent) or 1 (mild) and axillary temperature less than 37.5 °C (Table 3).

**Table 3 Tab3:** Outcome measures and endpoints

Efficacy	
Primary clinical endpoints	
Time to illness alleviation of influenza, defined as the time from baloxavir or oseltamivir administration until the following criteria were reached and sustained for at least 21.5 h (24 h—10%): both cough and nasal discharge/nasal congestion assessed as 0 (absent) or 1 (mild) and axillary temperature less than 37.5 °C	
Secondary endpoints	
Time to sustained resolution of influenza symptoms (cough, nasal discharge/nasal congestion) rated using the Influenza Symptom Severity Scale as absent (grade 0) or mild (grade 1) and resolution of fever (normal body temperature < 37.5 °C) for at least 72 h	
Time to resolution of fever (< 37.5 °C) for at least 12 h	
Time to sustained resolution of fever for at least 72 h	
Proportion of subjects with resolution of fever at each time point	
Time to resolution of all seven influenza symptoms (cough, sore throat, headache, nasal discharge/nasal congestion, feverish or chills, muscle ache or joint pain, and fatigue), rated using the Influenza Symptom Severity Scale as absent (grade 0) or mild (grade 1) for at least 21.5 h	
Time to resolution of each influenza symptom for at least 21.5 h	
Incidence of influenza-related complications (pneumonia determined by X-ray, bronchitis, sinusitis, otitis media)	
Incidence of influenza-related complications seen particularly in children (influenza-associated encephalitis or encephalopathy, febrile seizures, myositis) Incidence of death and hospitalization from influenza-related complications or influenza-related complications seen particularly in children	
Use of antibiotics	

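### The protocol does not separate stopping study drug from leaving the trial, so illness-related withdrawals may leave the primary endpoint unobserved and informatively censored

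*Protocol article*

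**What the plan says.** Two places in the Protocol article, both in Methods, Trial design, govern early exit.

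- The text after Fig. 1 opens "Reasons for discontinuation from the trial will include the following". The list contains a decision by the child or guardian, "death or any serious adverse event (SAE) or intolerance to study drug as determined by the investigator", a positive SARS-CoV-2 "test or suspected coronavirus disease 2019 (COVID-19"), repeated protocol deviation, and any other reason the investigator determines.
- The consent paragraph is permissive: the investigator may end a child's involvement "if the subject meets a newly developed or not previously recognized exclusion criterion that precludes further participation".

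The exclusion criteria in Table 1 include "Severe influenza symptoms requiring hospitalization", as well as convulsions and encephalitis or encephalopathy. The secondary endpoints in Table 3 include "Incidence of death and hospitalization from influenza-related complications or influenza-related complications seen particularly in children", with febrile seizures and encephalopathy among the named paediatric complications. Under Outcome measures and endpoints, an event that requires hospitalization is an SAE.

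Symptoms and temperature are recorded in the ePRO diary to Day 9 (Clinical and laboratory monitoring). The household questionnaire counts infections up to Day 10 or until the child leaves the study. Table 2 has a Discontinuation column (+14 days) marked for examination, vital signs, virus tests, questionnaire and adverse events. The two diary rows show no mark there. TTIA is summarised by Kaplan–Meier medians, with RMST to Day 9 as a secondary analysis (Statistical analysis).

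**The concern.** The listed reasons end participation in the trial, and the text has no separate category for a child who stops drug but stays under observation. A child who worsens and is hospitalized has an SAE. A child who convulses develops an exclusion criterion. A child with lingering fever or cough may be suspected of COVID-19. Each is likely to be a slow recoverer, and each may leave before alleviation is recorded.

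If such a child is then censored at withdrawal, Kaplan–Meier assumes that the child would have recovered like those still under observation. That makes the arm look faster than it was. A later analysis rule cannot repair this fully, because it cannot recover diary entries that were never made. Continued follow-up therefore has to be settled in the protocol. Investigators know the treatment and decide on most of these reasons, so the loss could also differ by arm.

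**Working it through.** **1. Overlap between exit reasons and outcomes**

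| Event after dosing | Route out of the trial | Also an outcome? |
|---|---|---|
| Hospitalization | SAE; Table 1 criterion on severe symptoms | Yes, Table 3, when due to the listed complications |
| Convulsions, encephalopathy | Newly developed Table 1 criterion; possibly SAE | Yes, Table 3 (febrile seizures, encephalopathy) |
| Suspected COVID-19 | Listed reason | Not an endpoint, but may reflect persistent fever or cough |
| Intolerance | Listed reason | Safety |

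**2. What remains observed.** The Discontinuation visit keeps examination, virology, the questionnaire and adverse events. TTIA depends on the diary, for which no entry at discontinuation is shown. Household infections are counted only until discontinuation.

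**3. Inputs for size**

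- From the documents: 134 and 66 children. This agrees with 2:1 allocation of 200, since 200 × 2/3 = 133.3 and 200 × 1/3 = 66.7. The median TTIA of 45 h is from two earlier single-arm baloxavir studies (Discussion).
- Not in the documents: any withdrawal rate, dropout allowance or shape of the TTIA distribution. These are assumptions.

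**4. Two illustrative models.** In both, one arm loses 1–10% of its children, all slow recoverers, who are censored at withdrawal.

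- Lognormal: median 45 h, log-SD 0.9, RMST to 192 h. Withdrawal falls at 24–72 h among children with TTIA above 96 h.
- Weibull: median 45 h, shape 1.0 or 1.5, follow-up to 216 h. Children withdrawn come from the slowest quarter.

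Bias in hours in the affected arm:

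| Withdrawn | Median, lognormal | Median, Weibull | RMST, lognormal | RMST, Weibull |
|---|---|---|---|---|
| 1% | −0.1 | −0.2 | −0.5 | −0.2 |
| 2% | −0.2 | −0.3 | −1.0 | −0.4 to −0.5 |
| 5% | −0.4 | −0.6 to −0.7 | −2.5 | −0.9 to −1.4 |
| 10% | −0.8 | −1.3 to −1.4 | −5.6 | −1.9 to −3.2 |

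**5. How extreme the upper rows are.** In the lognormal model, P(TTIA > 96 h) = 1 − Φ(ln(96/45)/0.9) = 1 − Φ(0.84) = 0.20. Withdrawing 5% of the arm therefore removes 0.05/0.20 = 25% of all slow recoverers, and 10% removes half of them.

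**6. Sampling error.** The SD of TTIA truncated at 192 h is about 50 h. The SE of the RMST difference is 50 × √(1/134 + 1/66) = 7.5 h, a 95% half-width of 1.96 × 7.5 = 14.7 h. The Weibull models give half-widths of about 10–17 h for the RMST difference and 13–20 h for the median difference.

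**The case against.** The case against is substantial, and much of it stands.

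- **Removal is not automatic.** The exclusion-criterion clause says the investigator may act, and only if further participation is precluded. SAE and intolerance are left to the investigator. Death ends follow-up under any plan. A reader might infer that non-informative censoring fails by rule; the text supports only that it is put at risk.
- **No censoring rule is printed.** That detail may sit in the full protocol or analysis plan, and its absence is not the point here. The point is the printed wording on leaving the trial, which determines whether data exist to analyse.
- **Antibiotics.** A reader might infer that a later infection needing antibiotics is a withdrawal reason. It is not. The criterion reads "Infectious diseases requiring systemic antimicrobial therapy and/or antiviral medicine (except anti-influenza medicine) at screening", so it applies at entry. The Treatment protocol section allows antibacterials for suspected infection after dosing, and antibiotic use is itself an endpoint.
- **Complications.** The event that triggers withdrawal is already observed and counted, and the Discontinuation visit adds an examination and adverse-event reporting. Only a further event after follow-up ends could be missed.
- **Difference by arm.** Five days of oseltamivir against one dose of baloxavir, with open-label judgement, makes unequal withdrawal plausible. But no rates by arm are given, and since the listed reasons end participation, intolerance after a single dose can end it too.
- **Table 2.** The layout was broken in extraction, and a home diary need not appear in a visit column. The blank suggests that diary follow-up stops but does not prove it.
- **Descriptive analysis.** No tests are planned, so no error rate or power is affected.

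What survives is that the text does not keep stopping drug apart from leaving the trial, and nothing in the article says the diary continues.

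**Conclusion.** The point holds as a weakness of low to moderate weight that is cheap to remove. As written, illness-related reasons may end observation of the primary endpoint, and the resulting estimates could be informatively censored in the direction that shortens the affected arm's TTIA.

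The primary median is fairly robust, with a shift of at most about 1.4 h even at 10% withdrawn. RMST is more exposed: about 0.2–1 h at 1–2%, 1–2.5 h at 5% and 2–6 h at 10%. All of this lies below the SE of about 7.5 h, but the bias is systematic and the confidence intervals do not reflect it.

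The figures rest on an assumed TTIA distribution with a 45 h median, on all withdrawals coming from slow recoverers in one arm only, and on censoring at withdrawal. The 5% and 10% rows are demanding, because they require a quarter and a half of that arm's slow recoverers to be withdrawn in the lognormal model.

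**What to change.** Reword Trial design to distinguish stopping study drug from leaving the trial:

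- Unless consent or assent is withdrawn, every dosed child continues the ePRO diary to Day 9 and, where feasible, the planned visits and household questionnaire to Day 10, whatever the reason for stopping study drug.
- Diary data recorded after stopping study drug are used in the TTIA analysis.
- A newly developed exclusion criterion bears on study drug only and does not end follow-up.
- As a sensitivity analysis, children who die or are hospitalized and have no later diary data are counted as not alleviated to Day 9.

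Mark the diary rows of Table 2 and the household-count wording to match. Decisions on treatment are unchanged. The cost is protocol wording plus a few more diary days and visits in the few children affected; no new procedure is needed.
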